### Safety assessments

Throughout the study, participants may encounter adverse events (AEs) related to acupuncture, including needle sickness, subcutaneous hemorrhage, hematoma, severe pain, infection, needle breakage, rash, and other symptoms. Additionally, during the administration of betahistine mesylate tablets, patients may experience gastrointestinal symptoms such as nausea, vomiting, and diarrhea, as well as allergic reactions like rash. All AEs will be meticulously documented in the Case Report Form (CRF), detailing the occurrence time (transient or persistent), severity (mild, moderate, or serious), possible causes (needle-related, medication-related, or non-needle-related), symptoms, duration, treatment measures, and resolution time. Prompt and appropriate treatment will be provided to participants experiencing mild to moderate AEs, with continuous monitoring by the attending acupuncturist. For serious AEs, immediate medical advice will be given within 48 h, and these events will be reported to the principal investigator and the research ethics committee within 24 h. Clinicians will determine whether to discontinue the trial based on the participant’s condition.

To evaluate differences in AEs between groups, statistical analyses using the Chi-square test or Fisher’s exact test will be conducted. This analysis aims to identify significant variations in the occurrence of adverse reactions between the treatment and control groups, thereby providing valuable insights into the safety of the interventions.

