Pathophysiologically, normal brain function relies on stable metabolic processes, and stroke-induced cerebral metabolic imbalances and secondary structural changes (14). In clinical practice, post-stroke vertigo patients often experience dizziness that is not related to positional changes but rather to prolonged physical activity or sustained attention, associated with cerebral blood flow dysregulation and subsequent oxygen and glucose imbalance (15). Moreover, following ischemic strokes, structural changes in the brain, such as alterations in white matter integrity and gray matter volume, have been well-documented. Studies indicate that structural abnormalities, including infarct location and total lesion volume, may be closely linked to the occurrence of vertigo after stroke (16). In particular, lesions involving the vestibular nuclei, brainstem, cerebellum, or vestibulo-cerebellar structures may be especially relevant to dizziness symptoms (17). Nevertheless, in patients with PCIS, the severity and persistence of dizziness may not be fully explained by lesion topography alone. Residual vertebrobasilar hypoperfusion, altered neurovascular regulation, and secondary reorganization of vestibular-related brain regions may also contribute to symptom burden during recovery (18). Therefore, in the present trial, lesion location will be documented at baseline, while TCD, sMRI, and ASL-MRI will be used as complementary tools to characterize dynamic cerebral hemodynamics, regional perfusion, and structural changes associated with symptom persistence and recovery.

Hence, this study designed as a multicenter, large-sample randomized controlled trial aimed at: (1) Primary objective: To evaluate the specific efficacy and safety of manual acupuncture for PCIS with vertigo or dizziness by comparison with sham acupuncture. (2) Secondary objective: To compare the effectiveness and safety of manual acupuncture with western medication (betahistine) for PCIS with vertigo or dizziness. (3) Mechanistic objective: To test the *a priori* hypothesis that acupuncture alleviates vertigo by improving posterior circulation hemodynamics and regional cerebral perfusion in vestibular-related brain regions. Changes in TCD parameters, ASL-MRI perfusion, and sMRI structural markers will be evaluated and correlated with improvements in DHI scores.

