**Figure 1 fig1:**
[figure not shown]
Research flow chart.

**Table 1 tab1:** Study schedule for data measurements.

Study period	Baseline	Allocation	Intervention period	Follow-up period
Time point (week)	−1	0	3	11
Enrolment and Baseline data:	Eligibility screen; informed consent; demographic characteristics; disease/combination medication history	Randomization		
Primary outcome:		DHI	DHI	DHI
Secondary outcomes:		DARS; dizziness diaries	DARS; dizziness diaries; adherence assessment	DARS; dizziness diaries
Objective hemodynamic/ imaging indicators:		TCDsMRIASL-MRI	TCDsMRIASL-MRI	
Other assessments:		Treatment expectations assessment	Safety assessment	Safety assessment

DHI, Dizziness Handicap Inventory; DARS, Dizziness and Anxiety Rating Scale; TCD, transcranial Doppler; sMRI, structural magnetic resonance imaging; ASL-MRI, arterial spin labeling MRI.

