### Randomization and blinding

A random number will be generated with the R software (V.4.3.3) and concealed in opaque random envelopes. The envelopes will be prepared by a third party in advance, with the sequence number labeled on the surface and the random number and group allocation information sealed in. The random envelopes will be preserved by special personnel who are not involved in treatment and evaluation. Participants are randomly assigned in a ratio of 1:1:1 to manual acupuncture (MA) group, sham acupuncture (SA) group, and western medication (WM) group.

Given the use of two distinct acupuncture techniques in this trial, the acupuncturist will be aware of the group allocation for each participant. However, identical auxiliary devices will be used in both the acupuncture and sham acupuncture groups to maintain blinding for participants. Participants in both groups will remain unaware of their specific group assignment. Furthermore, outcome assessors and statisticians will be blinded to group allocations throughout the study to minimize bias. To maintain blinding, all researchers will undergo identical training prior to the trial, and treatments will be administered in separate rooms for each participant. It should be noted that participants in the medication group will not be blinded.

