### Manual acupuncture (MA) group

The selected acupuncture points—Baihui (DU20), Fengchi (GB20), Wangu (GB12), and Taichong (LR3)—were determined based on preliminary literature review and consensus among acupuncture experts for this study. Detailed descriptions of each acupoint are provided in Table 2 and illustrated in Figure 2. All acupuncturists are licensed and have a minimum of 3 years of clinical experience. Prior to the trial, all acupuncturists will undergo training on acupoint positioning and manipulation techniques. Each sub-center will be assigned one acupuncturist who will be responsible for treating all patients at that center.

**Table 2 tab2:** Locations of acupoints.

Acupoints	Locations
Baihui (DU20)	On the median line of the head, 5 inches superior to the anterior hairline, at approximately the middle of the connecting line between the two auricular tips.
Fengchi (GB20)	On the posterior neck, inferior to the occipital bone, in the depression between the origins of sternocleidomastoid and the trapezius muscles.
Wangu (GB12)	On the posterior aspect of the head, in the depression between the mastoid process and the inferior nuchal line of the occipital bone.
Taichong (LR3)	0.5 to 0.8 finger breadths laterally to the dorsum of the foot, in the distal depression of the angle proximal between the 1st and 2nd metatarsa.

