### Western medication (WM) group

Betahistine mesilate tablets (6 mg per tablet; Eisai (China) Pharmaceutical Co., Ltd.; National Medical Products Administration No. H20040130) are used, one tablet each time, three tablets per day, after meals. The treatment was administered continuously for 5 days per week over a 3-week period.

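### The only role named for monitoring mild to moderate adverse events is an acupuncturist with no described contact with the medication arm, so the acupuncture versus medication safety comparison is open to unequal ascertainment

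*Protocol article*

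**What the plan says.** All references are to the protocol article.

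- **Monitoring (Safety assessments).** The section lists expected reactions to needling and to betahistine, and requires every AE to go into the case report form (CRF). It then states: "Prompt and appropriate treatment will be provided to participants experiencing mild to moderate AEs, with continuous monitoring by the attending acupuncturist". No other role is named for monitoring, and the medication arm has no separate provision.
- **Blinding (Randomization and blinding).** On the treating side, "the acupuncturist will be aware of the group allocation for each participant". On the assessment side, "outcome assessors and statisticians will be blinded to group allocations throughout the study", but AE collection is not assigned to these assessors. In addition, "participants in the medication group will not be blinded".
- **Contact by arm.** The manual and sham acupuncture sections each give five sessions a week for three weeks, 15 in all. The Western medication section describes only tablets ("one tablet each time, three tablets per day, after meals") and no session or visit.
- **Schedule (Table 1).** The entry "Safety assessment" stands at Weeks 3 and 11, without distinction by arm.
- **Analysis (Safety assessments).** AEs are compared between groups by chi-square or Fisher's exact test.
- **Role of safety.** The objectives in the Introduction put safety against sham in the primary objective and safety against betahistine in the secondary one. The abstract lists the AE rate among the secondary outcomes.

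**The concern.** A between-group test of AE counts is fair only if an event has about the same chance of coming to light in each arm. As written, two arms are seen face to face by a clinician on every treatment day and the third is not. The one person named to follow mild to moderate events belongs, on any described contact, to those two arms.

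If short-lived drug reactions such as nausea, diarrhea or rash go unreported more often than needling reactions seen on the day, two things can happen. Acupuncture may look less safe than betahistine when it is not, or a real safety advantage may be hidden. A smaller question concerns manual versus sham: the named monitor knows the allocation, and the CRF asks for a judgement of cause (needle-related, medication-related or non-needle-related).

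**Working it through.** **1. Scheduled contacts after Week 0**

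- Each acupuncture arm: 5 sessions × 3 weeks = 15, plus the Week 3 and Week 11 assessments, 15 + 2 = 17 (16 if the Week 3 assessment falls on a session day).
- Medication arm: 2.
- Manual versus sham: 15 against 15 sessions, so no difference.

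These are the contacts the article describes; others may exist.

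**2. Does the monitoring rule fit each arm?**

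| | Manual | Sham | Medication |
|---|---|---|---|
| Described contact with an acupuncturist | 15 sessions | 15 sessions | none |
| Common safety assessments | Weeks 3, 11 | Weeks 3, 11 | Weeks 3, 11 |
| Participant blinded | yes | yes | no |

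The rule is written for all participants but can be followed as described in two arms only.

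**3. What unequal ascertainment could do**

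The document gives no AE rate and no detection rate, so there is no figure of its own to reproduce, and everything in this step is illustration.

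- *From the document:* n = 78 per arm (Sample size calculation).
- *Assumed:* a true AE proportion p that is equal in both arms, and a ratio r of detection in the medication arm to detection in the acupuncture arm. Detection in the acupuncture arm is taken as complete.
- *Observed counts:* X ~ Bin(78, p) for acupuncture and Y ~ Bin(78, r·p) for medication.
- *Test:* pairwise chi-square without continuity correction, z = (X/78 − Y/78) / √(2·q(1 − q)/78), with q = (X + Y)/156. Reject if |z| > 1.96.
- *False-positive rate:* the sum of P(X = x)·P(Y = y) over all pairs (x, y) that reject.

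| True p, both arms | r = 1 | r = 0.9 | r = 0.75 | r = 0.5 |
|---|---|---|---|---|
| 10% | 5.2% | 5.7% | 8.8% | 22.6% |
| 20% | 5.1% | 6.3% | 13.3% | 42.7% |
| 30% | 5.0% | 7.0% | 18.8% | 62.2% |

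The excess lies almost wholly in the direction of acupuncture looking worse. At p = 20% and r = 0.5, for example, the observed rates are 20% and 0.5 × 20% = 10%.

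The same sum gives the chance of showing a real advantage. Take true AE rates of 10% with acupuncture and 25% with medication:

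| r | Observed medication rate | Chance of showing acupuncture safer |
|---|---|---|
| 1 | 25% | 72% |
| 0.9 | 22.5% | 58% |
| 0.75 | 18.75% | 35% |
| 0.5 | 12.5% | 7% |

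The result depends on r, which the documents do not give.

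**The case against.** The strongest reply is that the quoted sentence is not about detection. It concerns participants who already have an event, and says they are treated and followed. The sentence before it requires all AEs in the CRF, with no distinction by arm. Under Data management and confidentiality, researchers complete the CRFs, and someone outside the treatment reviews and enters them. Quality control promises SOPs and uniform recording. A journal article may also leave AE forms and interim contacts to the full protocol.

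Much of this stands, and it rules out several stronger readings that a reader might infer:

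- *That the medication arm never sees an acupuncturist.* No such statement is made. The manual acupuncture section even says: "Each sub-center will be assigned one acupuncturist who will be responsible for treating all patients at that center". Given where it stands, that most naturally means patients receiving needling, but it forbids the stronger claim.
- *That medication-arm events are caught only by recall.* Spontaneous reports are not excluded, and some participants are recruited as inpatients.
- *That AEs are recorded by an unblinded person.* The acupuncturist is named as monitor, not as recorder.
- *That manual versus sham is biased by unequal detection.* Both arms have the same sessions, with one acupuncturist per center.

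What the reply does not remove is the mismatch in the text. The section covers betahistine reactions, yet names only a role with no described place in the medication arm. A CRF can hold only events that come to light. The diary, as described, records dizziness episodes and acute medication, not AEs. This is a statement in the article that does not fit one arm, not a detail left for later.

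**Conclusion.** The point holds as a risk, not as a demonstrated bias. The monitoring sentence does not fit the medication arm, and the described contact is 15 sessions against none on top of two common assessments. The acupuncture versus medication AE test is therefore open to unequal ascertainment.

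The size cannot be estimated from the documents. Under the stated assumptions (78 per arm, equal true AE rates of 10% to 30%), the two-sided false-positive rate stays at about 6% to 7% when the medication arm's events are found 90% as often. It rises to between 23% and 62% when they are found half as often. Fisher's test, being more conservative, would give somewhat lower figures.

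The comparison affected is a secondary one. In manual versus sham, only possible unblinded monitoring or attribution of cause remains. The DHI analysis, the sample size and the significance level are untouched.

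**What to change.** 1. **Reconcile the text.** The monitoring sentence in Safety assessments and the description of the Western medication group must be brought into agreement, so that the stated arrangement covers all three arms. Who should monitor is for the investigators to decide.
2. **Use one common source of AEs.** Have participants in all three arms complete the same fixed AE checklist at Weeks 0, 3 and 11, and add the same AE line to the dizziness diary that all arms already keep. The Week 0 checklist separates nausea and vomiting already present with vertigo from later reactions. The diary line limits reliance on recall.
3. **Analysis.** Base the acupuncture versus medication AE test on this common source. Keep events observed at sessions in the full AE listing and in the manual versus sham comparison, where contact is equal and dropping them would lose information.

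The cost is one form, one diary line and a few sentences of protocol text; no visits are added. The downside is small: the medication comparison omits some minor events seen only at sessions, though they are still listed. The change does not remove differences in reporting that come from the medication arm being unblinded, which should be stated as a limitation of this comparison.

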### Patient recruitment

Recruitment strategies include poster, online platforms, and rehabilitation and neurology departments inpatients. Potential patients will be informed about the study specifics, including the purpose, subgroup allocation, interventions, treatment period, benefits, and potential risks. A neurology specialist will assess and diagnose interested patients to determine their eligibility. Eligible individuals who voluntarily choose to participate will be required to sign a written informed consent form prior to the start of the study. All patient information will be kept confidential. Participants have the right to withdraw from the study at any stage, with reasons for withdrawal being thoroughly documented.

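### The serious adverse event rule is inconsistent on timing and uses *serious* both as the top severity grade and as the reporting trigger

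*Protocol article*

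**What the plan says.** All the relevant text is in the Protocol article, section Safety assessments.

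- **Grading.** Every adverse event goes on the case report form with its "severity (mild, moderate, or serious"), along with timing, possible cause, symptoms, duration, treatment and resolution.
- **Lower grades.** "Prompt and appropriate treatment will be provided to participants experiencing mild to moderate AEs, with continuous monitoring by the attending acupuncturist". No reporting time is attached to this path.
- **Top grade, advice.** "For serious AEs, immediate medical advice will be given within" 48 h.
- **Top grade, reporting.** In the same sentence, "these events will be reported to the principal investigator and the research ethics committee within" 24 h.
- **Analysis.** Adverse events are compared between groups by a chi-square or Fisher's exact test. No separate test of serious events is named.

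No section of the article defines *serious* by outcome or lists seriousness as an item apart from severity.

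**The concern.** There are two defects in one short operative rule.

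The first is timing. The sentence on serious events describes one action, giving medical advice, in two ways that do not agree. A site that reads *immediate* and a site that reads 48 h would both believe they were compliant.

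The second is classification. Severity normally describes how intense an event is, and seriousness describes what it led to. Here a single three-level field carries both ideas, and the reporting rule hangs on its top level. Events can then be routed by intensity when the purpose of expedited reporting is to catch grave outcomes.

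What is at stake is participant protection and consistent classing of events across three centres. Safety is part of the primary objective (end of the Introduction), and the adverse event rate is named as a secondary outcome in the Abstract. Participants are post-stroke and in the non-acute stage, and they receive an antiplatelet or anticoagulant as appropriate (Intervention and comparison). Bleeding and haematoma are among the acupuncture-related events the section anticipates.

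**Working it through.** The plan gives no figure to reproduce, and the point uses no error rate, effect size or event count. The check sets the statements side by side.

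**Timing**

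| Action for a serious event | Limit stated |
|---|---|
| Medical advice | *immediate*, and also within 48 h |
| Report to principal investigator and ethics committee | within 24 h |

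1. Within the first row, the two descriptions apply to the same action and cannot both be the rule. This is the strict contradiction.
2. Between the rows, 48 h − 24 h = 24 h. As written, advice could be given up to a day after the reporting deadline has passed. The rows concern different actions, so both limits can be met together. The order is incoherent but is not a second strict contradiction.

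**Classification**

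The field has three levels, and the text divides them into two paths.

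| Grade recorded | Path stated | Reporting time stated |
|---|---|---|
| Mild | treatment, monitoring by the acupuncturist | none |
| Moderate | treatment, monitoring by the acupuncturist | none |
| Serious | medical advice, report | 24 h |

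Two kinds of event can be traced through this table.

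1. *Moderate intensity, grave outcome.* If graded by intensity, the event is moderate and enters the second row. Nothing in the stated rule moves it to the third row because of its outcome.
2. *High intensity, no grave outcome.* The section itself lists *severe pain* as a possible acupuncture-related event. The scale has no *severe* level, so the only level above moderate is *serious*. Using it sets off a report to the ethics committee.

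The single field can therefore misroute events in both directions. The first direction matters more, because it leaves out a report. The second adds reports.

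**What depends on the grade**

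The planned test compares adverse events between groups. An event counts as an adverse event at any of the three grades, so that comparison does not change with the grade. The sample size and the analysis of the primary outcome use no adverse event data.

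**The case against.** The strongest reply is that a journal article condenses a fuller protocol. The Quality control section promises standard operating procedures and training, and criteria for seriousness are commonly placed in such documents. Their absence here would not be a finding. That is correct, and the point does not rest on a missing definition. It rests on what the article states: a severity scale whose top level is *serious*, and two management paths split on that scale. A fuller document that kept the two concepts apart would conflict with this text.

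Other parts of the reply stand, and they limit what can be claimed. A reader might infer any of the following, but the document does not support them.

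- *The 48 h and 24 h limits contradict each other.* They apply to different actions.
- *Hospitalised events will be missed.* The article never discusses hospitalisation as an outcome of an adverse event. Hospital stay appears only as a recruitment source ("rehabilitation and neurology departments inpatients"). The case is a fair illustration of the rule, but how sites would grade such an event is not stated.
- *Serious event counts compared between arms will be wrong.* No such comparison is planned.
- *Events will be lost from the safety record.* All adverse events must be documented with symptoms, treatment and resolution. The gap is in expedited reporting.
- *Participants have had a recent stroke.* Entry requires more than 14 days since onset and a stable condition, with no upper limit on time since the stroke.

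The cause categories also overlap, since a medication-related event is also non-needle-related. The natural reading is needle, medication or other, and no stated analysis depends on it, so it is not part of this point.

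**Conclusion.** The point holds, within limits. The rule for serious adverse events contradicts itself on when medical advice is due, and it places that advice limit 24 h beyond the limit for reporting the same event. It also makes one word serve as a severity grade and as the trigger for expedited reporting, so an event graded moderate has no stated reporting time whatever it leads to.

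The number of events affected cannot be calculated, because the document gives no expected adverse event rates. The consequence for routing assumes that staff follow the published text and grade by intensity, as a field labelled severity invites. If an unseen procedure already separates the two concepts, the risk in practice is smaller, but the published rule still needs correcting.

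The correction should be made because it concerns participant protection and costs little. It does not bear on the efficacy conclusions or on the stated comparison of overall adverse events.

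**What to change.** 1. Reconcile *immediate*, 48 h and 24 h in the sentence on serious events, so that each action has one limit and the order of the actions makes sense. The limits are for the clinical team to set.
2. On the case report form, record severity (intensity) and seriousness as two separate items, with a severity scale that does not use the word *serious*.
3. State which of the two items triggers the report to the principal investigator and ethics committee, and align the wording of the lower-grade path with that choice.

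The cost is a wording change in the Safety assessments section and one extra case report form field, with the site procedures and training aligned to it. No change to sample size, randomisation or the planned tests is needed.

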**Discussion:**

This study will provide robust evidence on the safety and efficacy of acupuncture for vertigo with PCIS. In addition, it will test a prespecified biological hypothesis that acupuncture may relieve dizziness by improving vertebrobasilar hemodynamics and regional perfusion within vestibular-related brain networks, with corresponding imaging changes associated with clinical improvement. This research aims to offer novel insights into acupuncture as a potential therapeutic approach for vertigo following PCIS.

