### Sample size calculation

As reported in previous studies (8), the mean DHI score for patients treated with betahistine mesilate was 30. For the purpose of sample size estimation, we adopted the clinically meaningful difference derived from our primary comparison: manual acupuncture versus sham acupuncture, assuming a mean DHI score of 21 in the manual acupuncture group, 33 in the sham acupuncture group, with a standard deviation of 20. A 12-point difference in DHI total score between manual acupuncture and sham acupuncture was regarded as clinically meaningful, since the minimal clinically important difference (MCID) for DHI total score has been established as 11 points (26). The trial will include three groups in a 1:1:1 ratio. Using a twotailed test with a category 1 error of 0.05 and a statistical efficacy of 90%, One-Way Analysis of Variance (ANOVA) F-Tests was employed by PASS software (Power Analysis and Sample Size, version 15). The calculations indicate that a minimum of 66 participants per group is required, totaling 198 participants across all groups. Accounting for an estimated drop out rate of 15%, the total sample size should be increased to 234 participants, with at least 78 participants per group.

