### Statistical analysis

Analyses for this study will be conducted in accordance with both the intention-to-treat (ITT) principle and the per-protocol set (PPS) approach. The ITT analysis will include all randomized participants, and the missing data will be imputed using the Last Observation Carried Forward (LOCF) method, with the most recent observed data carried forward for filling. The PPS will include participants who have completed at least 80% of the prescribed treatment. SPSS 23.0 software will be used for statistical analysis. Quantitative indicators are described using mean, standard deviation, median, 25th percentile and 75th percentile. Categorical indicators are described using frequencies and percentages.

To control the Type I error caused by multiple comparisons, the Bonferroni correction will be adopted for pairwise comparisons of the primary outcome (DHI total score) among the three groups (manual acupuncture vs. sham acupuncture, manual acupuncture vs. western medication, sham acupuncture vs. western medication), with the adjusted significance level set at *p* < 0.017 (0.05/3); for secondary outcomes (DARS scores, dizziness diary indicators including attack frequency, duration and severity), the false discovery rate (FDR) method will be used for multiple comparison correction to balance the Type I and Type II error rates in exploratory analysis of multiple secondary indicators.

Since this study is a multicenter clinical trial, sub-center and corresponding baseline values were incorporated as covariates in the generalized linear model for analysis. Additionally, binary logistic regression was employed to analyze the impact of high versus low expectations on the primary efficacy endpoint across groups. The dependent variable in this analysis was response status, defined as participants showing at least a 50% reduction in total DHI scale score from baseline after 3 weeks of treatment (referred to as responders). The independent variable was the level of expectation (high or low).

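### A significance test on adverse events, in a trial sized on DHI alone, cannot by itself support the robust safety evidence that the abstract promises; the risk difference with its confidence interval should carry that conclusion

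*Protocol article*

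**What the plan says.** The objectives at the end of the Introduction put safety in the primary objective: "To evaluate the specific efficacy and safety of manual acupuncture for PCIS with vertigo or dizziness by comparison with sham acupuncture". The Discussion paragraph of the abstract states: "This study will provide robust evidence on the safety and efficacy of acupuncture for vertigo with PCIS". The abstract's Methods paragraph lists the AE rate among the secondary outcomes, and DHI is the sole primary outcome.

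For the between-group AE comparison, Safety assessments says: "To evaluate differences in AEs between groups, statistical analyses using the Chi-square test or Fisher’s exact test will be conducted". Its stated purpose follows: "This analysis aims to identify significant variations in the occurrence of adverse reactions between the treatment and control groups, thereby providing valuable insights into the" (the sentence ends on safety). The same section has the timing, severity, possible cause, duration, treatment and resolution of each AE recorded. Statistical analysis adds: "Categorical indicators are described using frequencies and percentages".

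Sample size calculation works from DHI means of 21, 33 and 30 with a standard deviation of 20, and after allowing for dropout concludes that "the total sample size should be increased to 234 participants, with at least 78 participants per group". No AE rate, safety margin or AE power appears in the document.

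**The concern.** Three statements fit together poorly: safety against sham is in the primary objective, the trial is said to yield robust evidence on it, and the one inferential tool named is a test for a difference, at a sample size chosen for a different endpoint. Such a test can flag a large excess of AEs. When it is non-significant at low power it says little, because it does not show which excess risks the data still allow.

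The contrast matters because a true difference is plausible. Real needles penetrate the skin and the sham needles do not. The protocol itself lists subcutaneous hemorrhage, hematoma and infection as possible acupuncture AEs, and the background treatment given to all arms includes aspirin or warfarin as appropriate. If the report had only a non-significant p-value beside the percentages, a reader could take more reassurance from it than the data give.

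**Working it through.** **The plan's own figure.** Inputs from Sample size calculation: means 21, 33 and 30, SD 20, and "Using a twotailed test with a category 1 error of 0.05 and a statistical efficacy of 90" percent, by one-way ANOVA F-test. The grand mean is 28 and the squared deviations are 49 + 25 + 4 = 78. The noncentrality is n × 78 / 20²; at n = 66 it is 66 × 78 / 400 = 12.87, which gives 90.05% power (65 per group gives 89.6%). Allowing for dropout, 66 / 0.85 = 77.6, so 78 per group and 234 in total. The stated figure reproduces. It contains no AE input.

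**Power of the AE test.** Inputs: 78 randomized per arm (from the protocol); two-sided 0.05 (assumed, since the protocol states alpha for DHI only); AE risks p₁ and p₂ (assumed, since none is given). Power is the sum, over all pairs of counts (i, j), of Bin(i; 78, p₁) × Bin(j; 78, p₂) for the pairs where the test gives p < 0.05. The miss rate is 1 − power.

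| Assumed AE risk, sham vs manual | Miss rate, Fisher | Miss rate, uncorrected Chi-square |
|---|---|---|
| 2% vs 6% | 90% | 77% |
| 5% vs 10% | 86% | 77% |
| 5% vs 15% | 53% | 43% |
| 10% vs 20% | 66% | 57% |
| 10% vs 30% | 14% | 10% |

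At the 66 per arm left after the assumed dropout, 5% versus 15% is missed in 62% (Fisher) or 50% (Chi-square) of trials.

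The answer depends on the base rate. Each doubling in the table is missed more than half the time. A tripling is mostly missed from 2%, missed about half the time from 5%, and mostly detected from 10%.

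**What a non-significant result can look like.** Suppose 11 of 78 manual and 4 of 78 sham participants have an AE.
- Risks: 14.1% and 5.1%; difference 9.0 points.
- Fisher p = 0.10; uncorrected Chi-square = 3.61, p = 0.057. Neither is significant.
- Wilson limits: 8.1% to 23.5% (manual) and 2.0% to 12.5% (sham).
- Newcombe lower limit: 9.0 − √[(14.1 − 8.1)² + (12.5 − 5.1)²] = −0.5 points.
- Newcombe upper limit: 9.0 + √[(23.5 − 14.1)² + (5.1 − 2.0)²] = +18.9 points.

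The p-value reports no significant difference; the interval shows that an excess of almost 19 points is not excluded.

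**Zero events.** With 0 of 78, the exact two-sided 95% upper limit is 1 − 0.025^(1/78) = 4.6%.

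**The case against.** The strongest reply is that the protocol contains no faulty decision rule. It says that the test looks for significant variations and offers insight; it nowhere says that a non-significant result will be taken as proof of safety. That stands. A reader might infer such a rule from the abstract's promise and the test's stated purpose taken together, but the text does not support more than the possibility.

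The second reply is that sizing on DHI alone is proper. A reader might infer from the primary objective that safety is a co-primary endpoint left without power. The document does not support this either: DHI is the sole primary outcome, the AE rate is secondary, and trials are not ordinarily powered for AEs.

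Third, safety does not rest on the test alone. AEs are recorded in detail and categorical data are summarized by frequencies and percentages. This also stands. The two tests are the only *inferential* AE analysis, not the only safety information; the summaries, however, carry no precision for the comparison between arms.

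Fourth, Chi-square and Fisher tests are conventional for AE incidence, and confidence intervals may be specified in an analysis plan that is not shown. Their absence is therefore no error in itself. What remains is that the protocol does state the analysis and its purpose, and that the stated method is weaker than the stated claim.

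Finally, the rates are assumed. At 5% versus 15% the expected AE count is 78 × (0.05 + 0.15) / 2 = 7.8 per arm, so the Chi-square test would ordinarily apply and the lower miss rate of 43% is the relevant one. A test that misses two in five such differences still cannot support a safety conclusion.

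**Conclusion.** The concern holds as a mismatch between claim, method and sample size. With 78 per arm the named tests miss 5% versus 15% about half the time (43% to 53%) and 5% versus 10% about four times in five (77% to 86%). Only a contrast as large as 10% versus 30% is detected reliably, with a miss rate of 10% to 14%. A non-significant result could not by itself be the robust safety evidence that the abstract announces.

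The figures rest on assumed AE rates, a two-sided 0.05 level and full follow-up of 78 per arm; with 66 per arm the test is weaker. The documents do not show that non-significance will be read as safety, and the efficacy analysis is unaffected. The matter is worth changing because it bears on what the trial may conclude about part of its primary objective.

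**What to change.** In Safety assessments, make the main between-arm safety analysis the risk difference with 95% confidence interval (Newcombe or exact) for participants with at least one AE and for participants with at least one serious AE. Give manual versus sham first and manual versus betahistine second. Keep the Chi-square or Fisher p-value as supplementary, and add a sentence that a non-significant result will not be taken as evidence of equal safety.

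In the abstract's Discussion paragraph, replace the claim of robust safety evidence with an estimate of AE frequency and its precision, noting for example that zero events in 78 participants leaves a two-sided 95% upper limit of about 4.6%.

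The cost is a few sentences and a few lines of code on data already to be collected, with no further patients or procedures. The downside is a more modest safety claim.
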